## **12 EFFICACY**

### **12.1 Primary Efficacy Endpoint**

Mean daily weight gain (g/d) over 16 weeks.

### **12.2 Secondary Efficacy Endpoints**

- Anthropometric measurements (head circumference gain velocity, length gain velocity) and Z-scores (weight for age, length for age, weight for length for age, head circumference for age)
- Formula intake volume

### **12.3 Exploratory Endpoint**

Markers of inflammation (tumor necrosis factor-alpha, interleukin 2, 4, 5, 6, 8, 10, 12, 13, & 17; interleukin 2 receptor, interleukin 1 beta, and interferon gamma).

## **13 LABORATORY DETERMINATIONS**

Central laboratories will be used for all laboratory determinations unless a special test or emergency testing is required. The central laboratories that have been contracted to perform these tasks adhere to Good Clinical Practices and will provide supplies and shipping materials for all laboratory determinations. Refer to the central laboratory manual(s) for additional information.

### **13.1 Biological samples**

A single blood sample (1.0 milliliters) will be collected from each subject via heel stick at the last study visit (visit 9) to assess markers of inflammation (tumor necrosis factor- alpha, interleukin 2, 4, 5, 6, 8, 10, 12, 13, & 17; interleukin 2 receptor, interleukin 1 beta, and interferon gamma). Stool samples will also be collected at the last study visit (visit 9) to assess stool composition (soap fatty acids).

Biological samples will be used exclusively for the purposes outlined in this protocol and for no other purpose.

## **14 STATISTICS**

### **14.1 Statistical Methods**

Analyses between cohorts (Brand Formula, BBN-001 w/ OPN, and BBN-102 w/o OPN) will occur separately depending on finalization of Generally Recognized as Safe (GRAS) approval of specific ingredients in BBN-001 w/ OPN formula.

#### **14.1.1 Primary Efficacy Endpoint**

The primary efficacy endpoint, mean daily weight gain (g/d) over a 16-week study period, will be compared between formula groups by the calculation of the 95% two-sided confidence interval on the difference between the two means. Non-inferiority will be determined if the lower limit of the two-sided 95% CI for the formula difference is greater than -3, assuming a non-inferiority margin of 3 mg/d.

Infant growth will also be descriptively summarized on the basis of the following sex-specific z- scores based on World Health Organization growth charts for infants and children ages 0 to 2 years of age: weight-for age, weight-for-length, length-for-age, and head circumference-for-age z-scores. For each subject, a line listing of all raw measures of weight, length, head circumference, and all z-scores (weight-for-age z-score, length-for-age z-score, weight-for-length z-score, and head circumference-for-age z-score) will be provided. Descriptive statistics will be used to summarize weight (kg), length (cm), and head circumference (cm) and all z-score data (weight-for age, weight-for-length, length-for-age, and head circumference-for-age) by formula group for each visit. A test for non-inferiority will also be performed for length gain (cm/d) velocity and head circumference gain (cm/d) velocity.

#### **14.1.2 Safety Endpoints**

A line listing of each subject with an adverse event will be generated. At the group level, the number and percentage of subjects having each AE will be summarized for each formula group. Secondary endpoints including stool characteristics, GI tolerance, and infant characteristics will be summarized using descriptive statistics and qualitatively compared to age appropriate reference values when appropriate.

#### **14.1.3 General Methods**

Continuous variables will be summarized using the appropriate descriptive statistics: n, mean, standard deviation, median, minimum, and maximum. The geometric mean will be presented for log-transformed

## **Clinical Protocol: BBN-IF-001**

variables. Frequency and percentage of observed values will be reported for categorical measures. A line listing of all data, sorted by subject and when appropriate by time, will be generated.

### **Analysis Populations**

- Intent to Treat (ITT): Subjects who are randomized to one of the formula feeding groups.
- Per Protocol (PP): A subset of the ITT population. It will consist of all subjects who complete the feeding protocol without major protocol violations and who consume a single non-study formula feeding no more than 10 times during the duration of 16-week study as documented on the Other Than Formula Feeding Log. Additionally, subjects who consume more than 3 complete days of non-study formula, defined as greater than 50% of the number of feedings in a 24-hour period from non-study formula, will also be excluded from the PP population.
- Safety Population: The safety population will be comprised of any subjects who are randomized and consume at least one feeding of the assigned formula.

Classification into ITT or PP populations will be conducted prior to the database lock. All listings will be provided for the ITT population. A separate listing will be included on the set of subjects who are randomized but never take any feeding formula before discontinuing from the study.

Since this study has a primary aim at demonstrating non-inferiority, the PP population will represent the primary analysis population to evaluate the treatment groups in terms of “efficacy”. All clinical outcomes (primary and secondary) will be subject to analyses using both the PP and ITT population.

### **14.2 Statistical Power and Sample Size Considerations**

In phase one, assuming a standard deviation in weight gain of 5.6 g/d (Nelson et al., 1989) and 80% power, 90 subjects per group (180 total) will be sufficient to demonstrate non-inferiority (one sided alpha = 0.025). Assuming a 25% attrition rate, a total of 256 subjects will be enrolled in this trial. Within each formula group, infants will be balanced by sex (equal number of males and females in each formula group). At the conclusion of the study, a post-hoc power analysis on weight gain will be conducted.

In phase two, the sample size for this study will be based on a non-inferiority test comparing weight gain velocity between Brand Formula and BBN-102 w/o OPN at Week 16. A non-inferiority margin of 3 g/d is set for the difference in weight gain for the two formula-fed groups (BBN-001 w/ OPN and BBN-102 w/o OPN).

A blinded interim analysis of 81 subjects who completed 16 weeks of the study was performed in phase one of the study to estimate the standard deviation of weight gain. Based on this analysis, it is assumed that the standard deviation in weight gain is 6.0 g/d. Assuming this standard deviation in weight gain of 6.0 g/d and approximately 90% power, approximately 168 (104 in the Brand Formula group and 64 in the BBN-102 w/o OPN group) will be sufficient to demonstrate non-inferiority (one-sided alpha = 0.025). Assuming a 25% attrition rate, approximately a total of 96 subjects will be enrolled in phase two of this trial.

The plan is to use the 129 subjects randomized to Brand Formula in phase one of the study, assuming a 25% attrition rate and 96 subjects meet the Per Protocol population criteria. This data has and will remain blinded through the enrollment of phase two of the study. In phase two of the study infants will be randomized to Brand Formula or BBN-102 w/o OPN in a 1:8 ratio. Assuming a 25% attrition rate and to obtain approximately 90% power, approximately 10 subjects randomized to Brand Formula and 86 subjects randomized to BBN-102 w/o OPN will be enrolled in phase two of the study. With the addition of the 129 subjects from phase one of the study, there will be approximately a total of 139 subjects enrolled in the Brand Formula group and 86 subjects enrolled in the BBN-102 w/o OPN group. Infants will be stratified by sex to achieve balance of males and females within each formula group.

### **14.3 Interim Analyses and Data Monitoring**

In phase one, an interim analysis will be conducted in a blinded manner when 128 infants (50% of the total goal sample size) had enrolled and completed Visit 5. Weight gain velocity (g/d) for all infants were reported descriptively (minimum, maximum, mean, median, standard deviation, first and third quartiles) for the following time intervals: enrollment to Visit 3, enrollment to Visit 5, Visit 3 to Visit 5. The purpose of the interim analysis was to determine whether or not the assumed standard deviation in weight gain velocity (5.6 g/d) based on reference data by Nelson et al., 1989, was appropriate for our study population. No unblinding or inferential statistics will be performed at the interim; as such, no alpha spending procedures were required.

An interim analysis will not be performed for phase two of the study.

## **15 SUBJECT IDENTIFICATION**

Subjects will be randomized and assigned a unique subject number. A subject number will never be reassigned or reused for any reason. The Investigator will maintain a master log linking the subject number to the subject's name. The Investigator will follow all applicable privacy laws in order to protect a subject's privacy and confidentiality. Information that could identify a subject will be masked on study material.

## **16 INVESTIGATIONAL PRODUCT ACCOUNTABILITY**

### **16.1 Formula Inventory**

The study site will maintain an Accountability Record of all formula received, dispensed, returned, or otherwise disposed of during the study. All dispensed and unused cans of study formula must be returned by the study subject's parent(s)/guardian(s) to the Investigator at the end of study. See Appendix E for details on investigational product accountability.

## **16.2 Formula Disposition**

If an infant discontinues participation in the study, the remaining formula will be returned to the study site. All investigational study formula returned will be disposed of in accordance with the instructions provided by the Sponsor.

## **17 RANDOMIZATION**

Formula-fed infants will be randomly allocated to one of the three study formulas (BBN-001 w/ OPN, Brand Formula, and BBN-102 w/o OPN) via RTSM (Randomization and Trial Supply Management) System. Randomization will be blocked by formula group and stratified by infant sex to achieve balance of males and females in each formula group.

## **18 ADVERSE EVENTS**

### **18.1 Definitions**

An adverse event (AE) is any untoward, undesired, or unplanned event in the form of signs, symptoms, disease, or laboratory or physiologic observations occurring in a person administered an investigational product in a clinical study. The event does not need to be causally related to an investigational product or participation in the clinical study. Any illness that a study subject develops during the study must be recorded on the AE case report form. Whenever possible, an illness should be recorded as a diagnosis rather than a series of symptoms.

Standardized definitions for stooling, spit-up, and crying (agreed upon by the Investigators and Medical Monitor; see Appendix F) will be used to report such symptoms.

All AEs must be assigned one of the following intensity scores:

- **Mild:** Transient or mild discomfort (< 48 hours); no medical intervention/therapy required
- **Moderate:** Mild to moderate limitation in activity, some assistance may be needed; no or minimal medical intervention/therapy required
- **Severe:** Marked limitation in activity, some assistance usually required; medical intervention/therapy required, hospitalization possible
- **Serious:** please see section 19.0.

All AEs must be assigned causality. The site PI or his/her designee will make a determination about the causality or relatedness of an AE to the investigational product (i.e. study formula) using the following categories:

**Related:** An adverse event (AE) that has a clear temporal association with investigational product administration (e.g., within 24 hours) and there is clear evidence of a causal relationship between the investigational product and the event.

---

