## **19 SERIOUS ADVERSE EVENTS**

A serious adverse event (SAE) is defined as an AE that:

- Results in death
- Is life-threatening, i.e., the subject was, in the opinion of the Investigator, at immediate risk of death from the event as it occurred (it does not include an event that, had it occurred in a more severe form, might have caused death)
- Results in a significant, persistent or permanent change, impairment, damage, or disruption in the subject's body function/structure, physical activities, and/or quality of life
- Requires in-subject hospitalization or prolongs hospitalization
- Is another medically significant event that, based upon appropriate medical judgment, may jeopardize the subject and may require medical or surgical intervention to prevent one of the outcomes listed above (e.g., allergic bronchospasm requiring intensive treatment in an emergency department or home, blood dyscrasias, or convulsions that do not result in hospitalization, or the development of drug dependency or drug abuse)

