| Constipation                           | Less than 3 bowel movements in 7 days                                                                                                                                                                                                                                                                                                                             |
| Acute diarrhea                         | Runny or watery stools for less than 2 weeks                                                                                                                                                                                                                                                                                                                      |
| Chronic diarrhea                       | Runny or watery stools for more than 2 weeks or  3 separate episodes of acute diarrhea in 2 weeks                                                                                                                                                                                                                                         |
| Spit-up, Vomiting, GERD issues  |                                                                                                                                                                                                                                                                                                                                                                   |
| Regurgitation                          | Milk comes up into mouth but never out of mouth AND infant DOES NOT: arch his/her back as if in pain, stop drinking even if hungry, or cry, wheeze, or cough related to feedings                                                                                                                                                                                  |
| Infantile spit up                      | Milk comes out of the mouth after feeding (typically non-forceful), and the amount that comes out is less than half of the feeding volume; non-projectile                                                                                                                                                                                                         |

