| Diaper rash                            | Contact/irritant dermatitis in the diaper area, with erythema and/or skin breakdown on the exposed convex skin surface (rate as Mild, Moderate, Severe using definitions outlined below)
Mild: Baby has an area of pinkness in the diaper area
Moderate: Baby has definite pinkness in a large area with some small areas of definite redness |

|                          |                                                                                                                                                                                                                                                                                                                |
|--------------------------|----------------------------------------------------------------------------------------------------------------------------------------------------------------------------------------------------------------------------------------------------------------------------------------------------------------|
|                          | Severe: Baby has intense redness over a large area of the perianal region, or any area of redness with skin breakdown in the diaper area                                                                                                                                                                |
| Atopic dermatitis/Eczema | Any new skin lesions, not in the diaper area. Score for any erythema, edema/papulation, and/or excoriation on scale from 0-3 each (9 points max). For each item, 0 = none, 1 = mild, 2 = moderate, 3 = severe.
Mild: 1 or 2 points
Moderate: 3 to 5 points
Severe: 6 to 9 points |

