### 11.1. Adverse Events

Adverse events (AE) summaries will only consider Treatment Emergent Adverse Events (TEAEs). TEAEs are defined as those adverse events with date of onset after formula intake and those existing adverse events that worsened during the study. If it cannot be determined whether the AE is treatment emergent due to a missing or incomplete (partial) onset date, the AE will be considered treatment emergent. Verbatim terms entered into the clinical database via the EDC system will be mapped to preferred terms and system organ classes using the Medical Dictionary for Regulatory Activities (MedDRA), version 23.0.

Each AE summary will be displayed by formula group. Summaries that are displayed by system organ class and preferred terms will be ordered by descending order of incidence of system organ class and preferred term within each system organ class. Summaries of the following types will be presented:

- Overall summary of the TEAEs which contain an overview of each item below.
- Subject count and incidence rate of TEAEs by MedDRA system organ class (SOC) and preferred term (PT).

- Subject count and incidence rate of TEAEs by MedDRA SOC, PT and highest severity. At each level of subject summarization, a subject is classified according to the highest severity if the subject reported one or more events.
- Subject count and incidence rate of TEAEs by MedDRA SOC, PT and closest relationship to study drug (Related/Not Related). Related AEs are those reported as “Related” or “Possibly Related”. At each level of subject summarization, a subject is classified according to the closest relationship if the subject reported one or more events. Adverse events with missing relationship will be considered related for this summary.
- Subject count and incidence rate of Serious TEAEs by MedDRA SOC and PT.
- Subject count and incidence rate of TEAEs leading to study discontinuation by MedDRA SOC and PT.

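### Protocol section 18.1 lists Serious as a fourth intensity score, so an SAE scored that way has no severity grade and the SAP's highest-severity tables cannot place it

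*Supplement*

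**What the plan says.** Protocol v5.2 section 18.1 introduces its grading rule with "All AEs must be assigned one of the following intensity scores" and lists four entries:

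- Mild: "Transient or mild discomfort (< 48 hours); no medical intervention/therapy required".
- Moderate: rests on some limitation of activity with little or no treatment; no duration is given.
- Severe: rests on marked limitation and ends "medical intervention/therapy required, hospitalization possible".
- Serious: has no description of intensity, only "please see section 19.0".

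Section 19 defines an SAE by outcome. One of its criteria is "Requires in-subject hospitalization or prolongs hospitalization". Section 20 requires all SAEs to go on the case report form and to reach the sponsor and medical monitor within 24 hours.

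Appendix F defines 13 common events. Two of them, diaper rash and eczema, carry their own three-grade scales with no time limit; Mild diaper rash, for example, is "Baby has an area of pinkness in the diaper area". SAP V4 section 11.1.1 repeats both scales.

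SAP V4 section 11.1 tabulates TEAEs by highest severity, so that "a subject is classified according to the highest severity if the subject reported one or more events". It plans serious TEAEs as a separate table. Section 11.1.1 also plans counts by highest severity for the events of special interest.

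**The concern.** Severity describes how intense an event was; seriousness describes its outcome or the threat it posed. An SAE can have any intensity, and a severe event need not be serious. If both share one field and only one entry may be chosen, scoring an event Serious discards its severity.

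Comparing adverse events between formulas is the primary safety objective, and the severity tables are part of that evidence. As the text stands, they cannot show how severe the SAEs were. Taking the highest grade per infant also presupposes an ordered scale, and Serious has no stated rank on it.

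**Working it through.** No figure in the plan bears on this point, so the check is a comparison of texts plus two counts.

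**1. Is the scale pick-one?** Yes. Section 18.1 asks for one score out of four, so Serious replaces a grade and does not add to it.

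**2. What can the SAP do with it?** SAP section 11.1 has a rule for a missing relationship (count as related) but none for a missing severity and none for the rank of Serious. Take an infant with one event scored Serious and one scored Mild. Three treatments are compatible with the text:

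| Treatment of Serious | Infant's highest severity |
|---|---|
| Ranked above Severe as a fourth grade | Serious |
| Merged with Severe | Severe |
| Treated as having no grade | Mild |

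The same data give three different table entries. The third moves an infant with an SAE into the lowest row; the second assumes an intensity that nobody recorded.

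**3. Which scale grades the skin events?** Appendix F has 5 stooling + 4 spit-up, vomiting and GERD + 2 crying + 2 skin = 13 terms. Two of 13 have a scale of their own beside the one in 18.1. Five days of slight pinkness is Mild in Appendix F but lies outside the 48-hour wording of Mild in 18.1. Neither document says in words which scale enters the severity table.

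**4. Is there a gap between Mild and Moderate?** Mild carries the 48-hour wording and Moderate needs some limitation of activity. An event of 48 hours or more with no limitation fits neither clearly.

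**5. Can the 48-hour wording be changed now?** Section 14.2 of the protocol puts 129 of about 139 Brand infants in phase one, which is 129/139 = 93%, and all of the roughly 86 BBN-102 infants in phase two. The earlier protocol in the supplement (section 20.1) uses the same four-entry scale, so phase-one events were graded under it. A new definition of Mild could reach BBN-102 events but almost none of the Brand events, and grading rule would then be confounded with formula. Deleting Serious does not have this effect: the other three definitions stay as they are, and the missing grade can be requested in both phases.

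**The case against.** **SAE capture is intact, and that stands.** A reader might infer that a hospitalised infant could be scored Severe, never be flagged as serious, and so miss the 24-hour report, since Severe mentions possible hospitalisation. The documents do not support this. Section 19 makes any event that requires or prolongs hospitalisation an SAE whatever its score, and the duty in section 20 follows that definition. Section 25 adds 100% source verification and medical-monitor review, and the SAP has its own serious-TEAE table. A hospitalised case recorded only as Severe would breach the protocol.

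**The case report form is not shown.** It may already hold a separate seriousness field. That would protect the serious-TEAE table. It would not supply an intensity grade for an event whose intensity field reads Serious.

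**Severity is tabulated, not tested.** Fisher's exact tests in section 11.1.1 compare incidence, and grading is blinded. No bias towards either formula is shown. This limits the weight of the point but does not make the tables well defined.

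**The 48-hour limit is open to two readings.** A reader might infer that constipation, chronic diarrhea and colic can never be Mild, and so that 5 of 13 special-interest terms are affected. That goes too far. The limit may qualify only transient discomfort. The 7 days in "Less than 3 bowel movements in 7 days" are a counting window for stools, not a duration of discomfort. Chronic diarrhea can also be met by separate short episodes. Only colic plainly spans weeks, and its crying is intermittent. A count of dictionary terms would in any case not measure affected infants.

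**The skin scales are specific instructions.** Appendix F tells sites to use its diaper-rash grades, its pointer to 18.1 sits within the remark on causality, and the SAP repeats both skin scales in the section that tabulates these events. The intended scale is reasonably evident; a sentence on precedence is all that is missing.

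**Conclusion.** The point holds for the structure of the scale. Section 18.1 mixes seriousness with severity in a single-choice field, and SAP V4 has no rule for the result. An event scored Serious has no severity grade, and the tables by highest severity in 11.1 and 11.1.1 cannot be derived reproducibly for an infant who has one.

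The size is every event stored only as Serious. The number is not in the documents and, in healthy term infants, is assumed to be small. The two skin terms need a statement of precedence. The gap at 48 hours or more without limitation needs one agreed reading, not a new definition. SAE reporting, the serious-TEAE table, the incidence comparisons and the growth endpoint are unaffected.

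This rests on one assumption: that the case report form follows the four-entry list in 18.1. If it already collects a three-grade intensity and a separate seriousness flag, only the wording needs correcting.

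**What to change.** - **Protocol 18.1:** delete Serious from the intensity list. Record seriousness as a separate yes/no against section 19 for every AE, including those scored Severe.
- **SAP 11.1 and 11.1.1:** tabulate severity as Mild, Moderate and Severe only, and keep serious TEAEs in their own table.
- **Stored data:** for any event held only as Serious, ask the site for an intensity grade before unblinding, in both phases and by the same procedure.
- **Skin events:** state in 18.1, Appendix F and SAP 11.1.1 that the Appendix F scales feed the severity tables for diaper rash and eczema.
- **48 hours:** leave the wording of Mild as it is. Note in the SAP that events of 48 hours or more without activity limitation fit no grade clearly, fix one reading while still blinded, and apply it to phase one and phase two alike.

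The cost is a wording change in two documents, one form field if seriousness is not already separate, and a few queries on existing SAEs. Grades obtained by query will be retrospective, which a table footnote should say.
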